**Methods:**

We propose to do a clinical trial in two stages with an adaptive trial design. In the first stage, participants with high blood pressure and proven low potassium intake (measured on the basis of a 24-h urine collection) will get individually tailored dietary advice, reinforced by weekly supportive phone/email support. At 4 weeks, if there has not been a measured increase in potassium intake, participants will be prescribed an additional potassium supplement. Testing will be conducted again at 8 weeks, to confirm the efficacy of the potassium supplement. Final measurements will be planned at 52 weeks to observe and measure the persistence of the effect of diet or additional supplement. Concurrent measurements of sodium intake, blood pressure, participant satisfaction, and safety measures will also be done.

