#### Stage 2: Potassium supplementation

Patients who are not able to successfully increase their potassium intake at 4 weeks with dietary counselling will be enrolled into stage 2. They will receive oral potassium supplementation in the form of 50 to 100 mmol of potassium citrate (25 to 50 ml of the liquid elixir based on the achieved 24-h urinary potassium). For those whose urinary 24-h potassium remains < 60 mmol/day, the dose of the supplement will be 100 mmol/day, and for those whose 24-h urinary potassium is between 60 and 90 mmol/day, the dose will be 50 mmol/day. In the DASH trial, the diet itself provides 120 mmol/day of potassium; however, the average measured 24-h urinary potassium was 2757 mg/day (~ 71 mmol/day). Hence, we are aiming for a higher dose of supplement to achieve the target outcome.

This dose of potassium is well tolerated in hypertension (reported adverse events, at < 1% frequency and not different from placebo, are change in bowel habits, belching and flatulence, and abdominal cramps with the current wax matrix-based and microencapsulated or coated microcrystal-containing preparations with extended release characteristics) [9, 20]. There are no reports of hyperkalemia reported in trials using this dose in a similar population [9, 13]. Potassium at this dose and formulation has excellent (> 90%) bioavailability [20]. This dose of potassium also should be effective in increasing urinary potassium to desired levels. There is also no comparator in this study since it is not a randomized controlled trial. Since potassium is well tolerated in hypertension, there will be no special criteria for discontinuing or modifying allocated interventions.

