### Outcomes

The primary outcome will be a successful increase in potassium intake to > 90 mmol/day as estimated from the 24-h urinary sample at 4 weeks. The secondary outcomes are persistence of increase in potassium intake (to > 90 mmol/day) at 1 year. For examination of safety, the following outcomes will be specifically examined: hyperkalemia (as defined as a serum potassium > 5.1 mmol/L) at 4 weeks after initiation of dietary counselling, at 1 and 4 weeks after starting potassium supplements, 1 week after dose escalation/dispensing, and at 12 months in everyone and gastrointestinal side effects (change in bowel habits, belching and/or flatulence; abdominal pain or cramps). Additional patient-reported adverse effects will also be measured and reported. Serious adverse events will be captured and reported as per regulatory requirements.

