### Measurements

The dietary intake of potassium will be assessed using 24-h collection of urine. There is a very close relationship overall between urinary potassium excretion and dietary potassium intake. There is a circadian variation [21] (more potassium excretion in the day than at night) which will be overcome with a 24-h urine collection. Twenty four-hour urinary sodium and creatinine (to assess for accuracy of collection) will also be measured for all participants at baseline, 4 weeks, and 52 weeks (end of study). In addition, participants who enrol into stage 2 will have an additional 24-h urinary collection and set of measurements at 4 weeks after initiation of the potassium supplement/dose escalation. Blood will also be collected at the same time points for measurement of kidney function and electrolytes (creatinine, sodium, potassium, total CO_2_, chloride). As an additional safety measure, serum potassium will be measured 1 week after starting potassium supplementation, 1 week after dose escalation, and 1 week post each re-dispensing visit. Blood pressure will be measured using automated oscillometric measurements and 24-h ambulatory monitoring. Additional assessment of adherence to supplement (apart from 24-h urine measures) will be made on the basis of returned pills/bottles. Patients satisfaction will be assessed using a simple 3 question survey (see supplementary material). Furthermore, all collected samples will be sent over to the laboratory for analyses. Any leftover samples will be discarded as medical wastes. There are no plans for subsequent or ancillary analyses for the future studies.

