### Sample size and analytical plan

The study goal is to estimate the success rate of the dietary intervention, as well as the success rate of the two-stage approach. Dietary counselling alone will not exceed this degree of increase which was seen with supervised intake and meal provision, but there are no robust data to support an estimate of its effect. However, potassium supplementation at the dose proposed would very likely result in achieved potassium intake of > 90 mmol/day in all participants. A sample size of 100 participants will allow us to able to estimate both success rates to within a margin of error of at most 5%. At 4 weeks, there should be little loss to follow-up; however, we estimate this to be about 20% to be conservative. Thus, this trial will enrol 120 participants. Furthermore, there are no plans for additional analyses including subgroup. Multiple imputation will be done for any missing data.

The primary outcome is a simple proportion of the participants who are able to achieve an increase in potassium intake. Secondary outcomes of the proportion of participants with persistent adequate potassium intake at 52 weeks, and safety outcomes, will also be reported as proportions. For the secondary outcomes of change in sodium, potassium, and blood pressure, the mean differences will be calculated and reported, and a paired *t*-test will be used to compare for statistical significance. There will be no interim analysis.

The proportions will be summarized as absolute numbers and percentages. Continuous outcomes will be reported as mean (and 95% confidence intervals). A *p* value of < 0.05 will be used for the paired comparisons of the continuous outcomes (i.e. secondary outcomes of change in sodium, potassium and blood pressure).

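### The 52-week persistence outcome is stated as one proportion across both stages, with no denominator or earlier-success rule, so it cannot show separately whether the diet effect and the supplement effect last

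*Protocol article*

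**What the plan says.** The abstract (Methods) gives the purpose of the last visit: "Final measurements will be planned at 52 weeks to observe and measure the persistence of the effect of diet or additional supplement". Two effects are named.

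The Outcomes section defines the matching endpoint: "The secondary outcomes are persistence of increase in potassium intake (to > 90 mmol/day) at 1 year". It gives a threshold and a time, but no stage, no denominator and no earlier time point.

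The section on sample size and analytical plan gives the summary to be reported: "Secondary outcomes of the proportion of participants with persistent adequate potassium intake at 52 weeks, and safety outcomes, will also be reported as proportions". The same section says that "there are no plans for additional analyses including subgroup". It also sets the overall goal: "The study goal is to estimate the success rate of the dietary intervention, as well as the success rate of the two-stage approach".

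Membership of the two stages is settled at week 4: "Patients who are not able to successfully increase their potassium intake at 4 weeks with dietary counselling will be enrolled into stage 2". Those who succeed on diet go on in follow-up with counselling only. The Measurements section provides a 24-h urine collection for everyone at baseline, 4 weeks and 52 weeks, and an extra one in stage 2 four weeks after the supplement is started or escalated. It also refers to serum potassium checks "1 week after dose escalation, and 1 week post each re-dispensing visit" and to adherence judged from returned pills or bottles.

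**The concern.** At week 52 the cohort holds two kinds of participant. Some reached the target by week 4 on counselling alone, and for them a reading above 90 mmol/day suggests that a change of diet has been kept up. The others did not reach it and were given a supplement on top of counselling. For them a high reading may reflect continued use of a product that, judging from the mention of re-dispensing visits, is supplied more than once. Both kinds of reading enter the same numerator.

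The second gap is the meaning of persistence. The text does not say whether the denominator is everyone enrolled, everyone measured at 52 weeks, or only those who had earlier exceeded 90 mmol/day. A participant at or below 90 at week 4 and again after starting the supplement, but above 90 at week 52, could be counted or left out.

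At stake is the trial's only stated measure of durability. A respectable 52-week figure could be carried largely by stage 2 while the diet effect has faded, or the reverse, and the planned report would not show which.

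**Working it through.** **The plan's own figure.** None is given for the 52-week outcome. The nearest statement is a margin of error of at most 5% for the two success rates with 100 participants. The worst-case 95% half-width at n = 100 is 1.96 × √(0.25/100) = 9.8 points, so that statement is not reproduced at p = 0.5. This is a separate matter and does not decide the present point. The 9.8 points serve below only as a yardstick for the cost of splitting.

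**Inputs.** From the article: 100 evaluable participants, the 90 mmol/day threshold, and assignment to stage 2 by failure at week 4. The article gives neither the number of diet successes nor any 52-week rate. I therefore assume D = 20, 30 or 50 diet successes out of 100, S = 100 − D in stage 2, and 60 participants above 90 at week 52.

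**Step 1: what the pooled figure identifies.** With d and s the 52-week rates in the two groups, the pooled count is D·d + S·s = 60. That is one equation in two unknowns, so s = (60 − D·d)/S.

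| D / S (assumed) | possible d | corresponding s |
|---|---|---|
| 20 / 80 | 0% to 100% | 60/80 = 75% down to 40/80 = 50% |
| 30 / 70 | 0% to 100% | 60/70 = 86% down to 30/70 = 43% |
| 50 / 50 | 10/50 = 20% to 100% | 50/50 = 100% down to 10/50 = 20% |

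Two concrete cases at 30/70 give the same pooled 60%:

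- diet 25/30 = 83% and stage 2 35/70 = 50%; 25 + 35 = 60
- diet 5/30 = 17% and stage 2 55/70 = 79%; 5 + 55 = 60

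**Step 2: how far the diet result can be hidden.** Assume 20 diet successes of whom 10 remain above 90, and 80 in stage 2 of whom 64 are above 90. The pooled figure is (10 + 64)/100 = 74%, while the diet figure is 10/20 = 50%. If all 20 diet successes are lost, the pooled figure is still 64/100 = 64%.

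**Step 3: which group is likely to be larger.** The article reports that measured urinary potassium in the DASH trial averaged about 71 mmol/day, below the target of 90. It expects counselling not to do better than supervised feeding, and it expects the supplement to bring all participants above 90. These statements suggest, without establishing it, that stage 2 will be the larger group and will dominate a pooled figure.

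**Step 4: precision if split.** Worst-case 95% half-widths, 1.96 × √(0.25/n): n = 20, ±22 points; n = 30, ±18; n = 50, ±14; n = 70, ±12; n = 80, ±11. Restricting stage 2 to those who exceeded 90 after starting the supplement would make its n somewhat smaller than S.

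**The case against.** The strongest reply is that this is a strategy trial. Its goal includes the success rate of the two-stage approach, and the abstract's wording about diet or additional supplement echoes the study's name and may mean the combined strategy. On that reading a whole-cohort proportion at 52 weeks is a legitimate result even if stage 2 drives it. This stands: a reader might infer that the pooled figure is uninformative, and it is not.

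Second, a reader might infer that no earlier success is required, so that late achievers count as persistent. The article does not say so. Its vocabulary, an increase that persists, leans towards earlier success. What can be said is that the rule and the denominator are undefined.

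Third, a reader might infer from the cited bioavailability above 90% that any swallowed dose appears in the urine whatever the diet. Bioavailability is not urinary recovery. The article's own example sets about 71 mmol/day measured in urine against 120 mmol/day provided by the diet. The point does not need this mechanism.

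Fourth, tabulation by stage is often left to a fuller document, and stage may not count as a subgroup. That would be enough if the article were merely silent. But it states the summary to be reported and says that nothing further is planned, subgroups included. If the investigators already intend a split, one sentence saying so removes the difficulty.

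**Conclusion.** The point holds in a limited form. As stated, the 52-week outcome is one proportion without a stage split, a denominator or an earlier-success rule. It can answer whether the strategy leaves participants above 90 mmol/day at one year. It cannot answer separately whether the diet effect and the supplement effect last, which is the purpose the abstract gives.

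The size cannot be taken from the documents, because they give no 52-week rates. Under the assumed 60/100 with a 30/70 split, the diet rate could lie anywhere from 0% to 100%. That shows a failure to identify the components; it does not predict a bias. The fault lies in the outcome definition and analysis wording, not in the design or data collection. It concerns a secondary outcome and should be corrected, but it does not threaten the primary result.

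**What to change.** Keep the proportion of the whole cohort above 90 mmol/day at 52 weeks as the strategy result, and label it *adequate at 52 weeks* rather than persistent. Add two proportions, each with its denominator and a 95% confidence interval:

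- (a) among week-4 diet successes, those also above 90 at week 52;
- (b) among stage 2 participants above 90 at the collection four weeks after supplement start, those also above 90 at week 52, described by whether they were using the supplement at week 52 according to the dispensing and returned-bottle records.

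State that this split by stage is planned and is not excluded by the sentence on subgroups. Since stage 2 adds the supplement to counselling and there is no comparator, describe (b) as persistence on counselling plus supplement.

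The cost is in wording only, because the urine collections and adherence records already exist. The intervals will be wider than the worst-case ±9.8 points for 100 participants: about ±18 at n = 30 and ±22 at n = 20, both sizes assumed. Both (a) and (b) condition on one high reading, so they will fall somewhat through day-to-day variation alone, and the report should say so. The whole-cohort proportion does not have that problem.

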## Methods

### Study design and setting

The study design is a single-centre, single arm clinical trial, with an adaptive design of two possible sequential interventions. For the dietary advice, this is outside the phases which apply to pharmacological trial regulatory description. The potassium supplement aspect could be considered as a phase 2, since, though approved for other indications, they have not been approved for hypertension. Focused and individualized dietary counselling to increase potassium intake will be the initial intervention amongst hypertensive individuals with low potassium intake. The aim of the study is to find the most effective intervention to increase potassium intake in this population. Since diet is the only recommendation in current clinical practice guidelines, this will be the initial intervention. Only in participants who do not achieve an increase in potassium intake, as measured on the basis of her 24-h urine potassium, as described below, will a potassium supplement be added. From a safety perspective, this was thought to be the most suitable study design. A comparison of a potassium supplement with a diet might result in a change in diet in patients randomized to a supplement, with possible safety issues in terms of hyperkalemia. Hence, the study design is a two-stage intervention, of dietary counselling, with the second stage of supplement only added to those in home the dietary counselling has been insufficient in increasing potassium intake (Figs. 1 and 2).

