**Fig. 2 Fig2:**
[figure not shown]
Stage 2 study period content for participants who failed stage 1, including the schedule of enrollment, interventions, and assessments for the Diet or Additional Supplement to Increase Potassium study

This study and patient recruitment will take place in a referral hypertension clinic at a tertiary care teaching hospital. Patients with difficult to control hypertension are referred to this clinic, and all patients undergo evaluation of their sodium and potassium intake with a 24-h urinary collection. The study coordinator will obtain written informed consent and to ensure that all necessary information is obtained. During the consent process, the study coordinator will ensure that there are no overtures of coercion, duress, or undue incentive. On the consent form, participants will also be asked if they agree to use their data should they choose to withdraw from the study.

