### Study population and timeline

In this trial, all patients with low dietary potassium intake will be eligible for enrolment. The study coordinator will screen patient for eligibility and obtain informed consent. Patients known to be at risk for hypokalaemia or hyperkalaemia will be excluded. The estimated duration for this study is 4 years.

Inclusion criteria:

(1) Hypertension (either on treatment, any level of BP; or not on treatment with an ambulatory blood pressure monitoring (ABPM) with daytime systolic blood pressure (SBP) > 140 or diastolic blood pressure (DBP) > 90)

(2) Aged 18 and greater

(3) 24-h urine potassium < 60 mmol

Exclusion criteria:

(1) Serum potassium < 3.3 or > 5.1 mmol/L

(2) Glomerular filtration rate (GFR) < 45 ml/min/1.73 m^2^

(3) Primary hyperaldosteronism

(4) Pregnancy

(5) Psychiatric disorder which, in the opinion of the investigator, would interfere with the study, or inability to give consent

(6) Severe liver disease

(7) Metabolic alkalosis (HCO_3_ > 32 mmol/L)

(8) Exclude patients who need to be started on renin-angiotensin-aldosterone blockade in the next 3 months

(9) Gastrointestinal disorder (delayed gastric emptying, dysphagia, gastric/duodenal/oesophageal ulcers)

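### If the 24-h urine that qualifies a participant is also the baseline, regression to the mean biases the paired test of potassium change upward and can by itself give p < 0.05

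*Protocol article*

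**What the plan says.** - **Entry.** The inclusion criteria (Study population and timeline) require "24-h urine potassium < 60 mmol", and the same section says that "all patients with low dietary potassium intake will be eligible for enrolment". No repeat or averaged qualifying value is mentioned.
- **Source of the qualifying value.** Study design and setting says of the referral clinic that "all patients undergo evaluation of their sodium and potassium intake with a 24-h urinary collection".
- **Study collections.** Measurements says that 24-h urinary sodium and creatinine, alongside potassium, "will also be measured for all participants at baseline, 4 weeks, and 52 weeks (end of study"). Stage 2 participants give a further collection 4 weeks after the supplement starts. Whether the baseline collection is the clinic's qualifying one or a new one is not stated.
- **Design.** "The study design is a single-centre, single arm clinical trial", and "There is also no comparator in this study since it is not a randomized controlled trial".
- **Analysis.** Sample size and analytical plan says "For the secondary outcomes of change in sodium, potassium, and blood pressure, the mean differences will be calculated and reported", tested by paired t-test at p < 0.05. It does not name the pairs of time points.
- **Stage 2.** "Patients who are not able to successfully increase their potassium intake at 4 weeks with dietary counselling will be enrolled into stage 2". The Abstract adds that the 8-week testing is meant to confirm that the supplement works.

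**The concern.** The entry criterion is a cut-off on the variable whose change is later tested. A 24-h urinary potassium varies from day to day within a person. A group picked because the value was below 60 contains some people who happened to be low that day, and their next collection is on average higher whatever is done to them. With no control arm, nothing in the design separates this rise from an effect of counselling. If the change is measured from the qualifying value, zero is the wrong reference for the t-test, and a small p value could be read as evidence of efficacy when selection alone might have produced it.

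The same selection recurs at week 4. Only participants with a low 4-week value enter stage 2, so a comparison of week 8 with that value would also lean upward.

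**Working it through.** **The plan's own figure.** There is none to reproduce. The protocol gives no SD, within-person correlation, effect size or power for the paired test. The only sample-size input used here is enrolment of 120 with 20% loss: 120 × 0.8 = 96 pairs. Using the plan's 100 evaluable participants instead would raise each t by a factor of √(100/96) = 1.02.

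**Assumptions, none of them from the documents.** Clinic mean μ = 50 to 70, between-person SD σb = 18 to 22, within-person SD σw = 8 to 22 mmol/day, normal distributions, no true change, and the qualifying collection used as baseline.

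**Formulas.**
- Total variance s² = σb² + σw²; correlation between two collections ρ = σb²/s².
- a = (60 − μ)/s; λ = φ(a)/Φ(a); mean of the selected values = μ − sλ.
- Expected rise with no effect = (1 − ρ) × sλ.
- Variance of the change = (1 − ρ)² s²(1 − aλ − λ²) + s²(1 − ρ²).
- Expected t = rise ÷ (SD of change/√96). The two-sided 5% critical value on 95 df is 1.985.

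**Low end** (μ = 50, σb = 22, σw = 8):
- s² = 484 + 64 = 548, s = 23.41, ρ = 484/548 = 0.883.
- a = 10/23.41 = 0.427, λ = 0.547, selected mean = 50 − 12.8 = 37.2.
- Rise = 0.117 × 12.8 = 1.5 mmol/day.
- Variance of change = 3.5 + 120.5 = 124.0, SD 11.1.
- t = 1.5/(11.1/9.80) = 1.3, below the critical value.

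**High end** (μ = 70, σb = 18, σw = 22):
- s² = 324 + 484 = 808, s = 28.43, ρ = 324/808 = 0.401.
- a = −10/28.43 = −0.352, λ = 1.035, selected mean = 70 − 29.4 = 40.6.
- Rise = 0.599 × 29.4 = 17.6 mmol/day.
- Variance of change = 85 + 678 = 763, SD 27.6.
- t = 17.6/(27.6/9.80) = 6.2, far above the critical value.

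**Chance of a significant rise with no effect.** A separate grid (mean 50 to 80, total SD 20 to 30, ρ 0.3 to 0.95, n = 100) gives 0.12 to 1.00. At mean 60 and SD 25 it is 0.99 for ρ = 0.5, 0.90 for ρ = 0.7 and 0.44 for ρ = 0.9. The nominal upper-tail rate is 0.025.

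**Separate baseline.** In a lognormal simulation with n = 100, in which the baseline was a new collection after selection, the mean change was 0 and the chance of a significant rise was about 0.025.

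**Primary outcome.** Under the assumptions above, between about 0% and 12% of those selected below 60 exceed 90 mmol/day on a second collection by chance.

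**Stage 2.** With mean 60 to 70, σw = 12 to 22, an assumed diet effect of 15 to 40 mmol/day and no supplement effect, the mean rise from week 4 to week 8 among those at or below 90 at week 4 is about 1 to 18 mmol/day.

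**The case against.** **The baseline may be a fresh collection.** Measurements lists a study baseline, and the clinic's routine urine is described elsewhere. Nothing says that they are one sample. The schedule sits in two figures that are not reproduced in the text reviewed here, and the full protocol may settle it. This stands, and it is why the point is conditional. What remains is that the article fixes the test and its threshold without excluding the biased comparison.

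**Significance is not assured.** A reader might infer that the test is bound to come out significant, or that its null hypothesis is false by design. The documents do not support either. They give no mean, SD or correlation. They also describe usual potassium intake as low and cite about 71 mmol/day as the urinary value measured on a potassium-rich trial diet, so an untreated clinic mean near 70 may be generous. With a mean of 50 and little day-to-day variation, the expected t falls below the critical value.

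**It is a secondary outcome.** This is correct. The stated goal is to estimate success rates, and the primary outcome is a simple proportion above a cut-off 30 mmol above the entry limit. A reader might infer that the primary result is equally compromised, but the working shows a much smaller effect there.

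**No week 4 to week 8 test is specified.** This is also correct. The analysis section names no such pair and rules out subgroup analyses. The possible bias is also modest beside a planned supplement of 50 to 100 mmol/day. The stage 2 remark is therefore only a caution, prompted by the purpose that the Abstract gives to the 8-week testing.

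**Conclusion.** The point holds conditionally. Selection below 60 mmol, a single arm and an uncorrected paired t-test are all stated. Whether they combine into a biased test depends on whether the qualifying collection is the baseline, which the article leaves open. If it is, the potassium change is biased upward by about 1.5 to 18 mmol/day under the stated assumptions. The expected t then ranges from not significant (1.3) to overwhelming (6.2), and a p value below 0.05 could not be read as an effect of the intervention. If the baseline is a separate collection, this bias disappears. The finding concerns a secondary outcome and needs a clarification of the plan. It does not undermine the primary proportion.

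**What to change.** In Sample size and analytical plan:

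- State that change in urinary potassium is computed from a baseline 24-h collection taken after eligibility is fixed and separate from the qualifying one.
- Where a participant has no such collection, report the change descriptively, with no p value and no attribution to the intervention.
- If a week 4 to week 8 change in stage 2 entrants is reported as evidence on the supplement, do not test it against the 4-week value that triggered entry. Report the week-8 level and the proportion above 90 mmol/day, each with a confidence interval.

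Subtracting an estimated regression to the mean is not a workable substitute. It needs the mean and variance of the unselected clinic population, and the trial's later collections are all taken under intervention.

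For participants already enrolled, the cost is wording, plus the loss of those without a separate baseline from the tested comparison; they contribute descriptive data only. If separate baselines are not being collected now, obtaining them for new participants means one more 24-h urine each.
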